## Abstract

**Objectives:**

In this protocol, we describe a planned intervention to adapt the Mother Mentor (MoMent) peer support program for women living with HIV (WLWH). WLWH face a six-fold higher risk of cervical cancer, yet screening and treatment rates remain low in Nigeria.

**Methods:**

Using an implementation science approach, we will engage key stakeholders—including ministries of health, NACA, professional bodies, WLWH, Mentor Mothers, healthcare providers, and development partners (e.g., WHO, US CDC, USAID)—through deliberative democracy to adapt and expand MoMent for home-based HPV screening and follow-up treatment. We will pilot the adapted MoMent HIV+HCC program with 1,500 women in 15 health facilities across Nigeria’s five geopolitical zones. The RE-AIM framework will guide evaluation of reach, adoption, fidelity, effectiveness, and sustainability.

**Results:**

This study is designed to contribute to WHO’s global strategy to eliminate cervical cancer by improving access to home-based screening and care in low-resource settings.

**Conclusion:**

Findings will inform national HPV prevention efforts and may drive broader integration into Nigeria’s cervical cancer program.

**Clinical Trial Registration:**

Clinicaltrials.gov, identifier NCT06751030.

## Introduction

Cervical cancer (CC) is the fourth most common cancer in women globally, with 660,000 new cases and 250,000 deaths in 2022 [1]. Africa hosts 19 of the top 20 countries with the highest incidence [1]. Women living with HIV (WLWH) are at six times higher risk of developing CC [2, 3], and it remains the most common AIDS-defining malignancy [4]. Limited access to screening and treatment accounts for 90% of CC deaths globally [5].

Despite improvements in HIV care, CC risk among WLWH in Nigeria remains unchanged over the last two decades [1, 2]. In Nigeria, CC is the second most common cancer in women, with over 12,000 new cases and nearly 8,000 deaths per year. The government has recently prioritized CC control, initiating HPV vaccination for girls aged 9–14 [6, 7]. However, these efforts do not address the screening needs of adult WLWH.

Cytology-based screening methods like Pap smears are impractical in low and middle income countries (LMICs) due to cost and infrastructure demands [8–10]. Less resource–intensive screening approaches have shown success in detecting and preventing disease [3]. These include visual inspection with acetic acid/Lugol’s iodine (VIA/VILI) [4] and self-collection (SC) tests targeting HPV, the causative agent of CC [5, 6, 11].

HPV SC requires less infrastructure than cytology-based methods, improving accessibility. In sub-Saharan Africa (SSA), 60%–75% of women who develop CC live in rural areas without early screening and treatment facilities [7–9]. Programs delivering services closer to these areas could dramatically expand access and reach underserved populations. HPV self-testing also reduces loss to follow-up common in cytology-based programs. SC samples are suitable for HPV detection [10] and have comparable sensitivity and specificity to provider-collected samples [12].

Nigeria’s MoMent peer-support program, originally designed to improve HIV care, pairs experienced WLWH (who become Mentor Mothers, MMs) with newly diagnosed peers. MoMent significantly improved ART adherence and viral suppression [13] and now operates nationally. Peer support programs like MoMent have positively influenced health-seeking behaviors and care utilization in low-resource settings [14–17], making it an ideal model for a screening intervention. The CHESS (Community, Home-based Education, Screening Services) study builds on MoMent by integrating HPV self-screening into community HIV care.

### Study Aims

1. Use a stakeholder deliberation (SD) conference methodology to adapt the MoMent program to promote home-based HPV cervical cancer screening (HCC) and follow-up treatment for HIV positive women.2. Implement the MoMent HIV+HCC cervical cancer screening program and assess program reach, effectiveness, adoption, and fidelity.3. Conduct post-implementation process evaluation of barriers and enablers to program maintenance.

To date, we have completed Specific Aim 1, including the deliberative democracy process, adapting the intervention, and training study personnel for implementation. We have also initiated a soft roll-out of the intervention in Aim 2. The remainder of this protocol outlines details for Specific Aims 2-3.

## Methods

### Overview

This implementation science study evaluates an adapted peer-support/lay-health intervention to increase HPV testing among WLWH and examines implementation, clinical outcomes, and sustainability metrics.

Our implementation process for the adapted MoMent HIV+HCC intervention involves: 1) facilitating SD conferences to collect input on how to adapt the MoMent program for CC control activities; 2) creating and implementing the HIV+ HCC intervention for the MoMent program; 3) measuring reach, adoption and implementation metrics at 6-month after intervention commencement; and 4) measuring intervention maintenance 18 months after intervention commencement. At the time of submitting this protocol, SD conferences were held and the intervention is adapted. We will conduct intervention activities through connections with clinics and existing MoMent programs across 15 clinics in eight Nigerian states.

	Proportion of MMs who attained at least a “competent” score on their performance review at 6 & 18 months	Number of MMs who attained a “competent” score on performance review	All MMs who have seen at least 12 weeks of service at 6-month follow-up	Performance review	2, 3	6 months, 18 months
	Proportion of patients treated within 2 weeks of SC sample received at 6 months	Number of WLWH treated within 2 weeks of SC sample received at clinic	Number of WLWH who test positive for HPV 16/18/45	Medical records review	2	6 months
	Fidelity to intervention as planned – proportion of complete MM checklists completed by MMs at 6 months	Number of checklists showing 4 of 6 steps completed for each MM encounter	All MMs who have seen at least 12 weeks of service at 6-month follow-up	MM logs/Employment records	2, 3	6 months, 18 months
Maintenance	Proportion of clinics that maintain target ratio of patient to MM maintained at 18 months	Number of MMs employed (retained or newly recruited/trained)	Number of eligible WLWH being treated at clinics	Employment records/Medical records	3	18 months
	Proportion of clinics conducting ongoing MM refresher trainings at 18 months	Number of annual trainings conducted in each clinic	Number of clinics	Training records	3	18 months
	Proportion of clinics sustaining optimal test to treatment window at 18 months	Number of clinics with optimal test to treatment window	Number of clinics	Medical records review	3	18 months

Aim 1Use SD methodology to adapt the MoMent program to promote home-based HPV cervical cancer screening (HCC) and follow-up treatment for WLWH.

Aim 1 comprised the formative work that is the foundation for the CHESS study. We focused the adaptation of the MoMent intervention for CC screening on constructs of the CFIR framework deemed by Means and colleagues to be especially relevant to LMIC settings [24]. SD approaches offer a way to engage communities in adoption and expansion of programs such as CC screening [13, 25–30]. Stakeholders include policymakers, clinic administrators, clinicians, HIV peer-support leaders and WLWH. We employed an innovative two-day, SD conference in which participants viewed neutral informational briefings and gained insights into competing advantages and disadvantages related to CC screening approaches to inform their perspectives. Stakeholders then deliberated and reached consensus on feasible adaptation strategies.

Qualitative data collection included deliberation session recordings, transcripts and participant generated pro-con lists of considerations, created during the deliberation. We also held pre- and post-deliberation surveys to assess changes in participant knowledge and attitudes related to CC prevention for WLWH.

Simultaneous to the community SD, we held a one-day expert stakeholder meeting for high-level Nigerian decision makers, including federal stakeholders (e.g., Ministry of Health, National Cancer Control Programme, National Agency for the Control of AIDS), development agencies and implementing partners (e.g., World Health Organization, Centers for Disease Control and Prevention, and USAID). This expert session introduced decision makers to the CHESS study, shared preliminary planning and the outcomes of the SD community process, and solicited feedback on the study plan. This meeting also allowed for buy-in from expert stakeholders, several of whom were asked to sit on the study’s technical advisory group.

Findings from the SD conference were used to adapt the CHESS intervention based on the considerations raised by community deliberators and expert stakeholders. Two key changes to the study protocol were made as a result:

Major Change 1: HPV education and screening were moved from home to community-based locations.

Major Change 2: High-risk HPV results were determined better returned by MMs rather than by nurses to maintain the relationship with patients and help facilitate next treatment steps for patients with high-risk results.

Aim 2Implementation and Assessment of Reach, effectiveness, adoption, and fidelity.

The details of Aim 2 are provided below and summarized in Figure 1.

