**FIGURE 1 F1:**
[figure not shown]
Aim 2 implementation flow chart (CHESS: Community, Home-based Education, Screening Services, Nigeria, 2025).

We will implement the adapted MoMent HIV+HCC program in 15 Nigerian clinical sites to recruit 30 MMs and 1500 WLWH for mid- and post-implementation assessments of reach, effectiveness, adoption, and fidelity. Implementation outcomes will be evaluated 6 months post-implementation with mixed methods. Key outcomes include reach and effectiveness, as indicated by eligible women touched by the HIV+HCC intervention, uptake of screening, women with high-risk HPV (hrHPV) 16/18/45/other genotypes treated, persistent or recurrent hrHPV post-treatment, and correlation of disease persistence with CD4 count and HIV viral load. We will measure program adoption outcomes that include training of MMs, WLWH who return a SC sample, and participating clinics’ integration of MoMent HIV+HCC into routine practice. We will gauge implementation fidelity as indicated by peer leaders’ progress reports. We will also measure system barriers and added cost of CC screenings.

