#### MoMent HIV+HCC Adapted Intervention

The MoMent HIV+HCC adapted intervention will consist primarily of MMs supporting WLWH in testing for hrHPV. MMs will be responsible for recruiting and enrolling WLWH into the study, educating them about HPV and SC, transporting samples to the clinic/laboratory, returning testing results and facilitating treatment for WLWH who need follow up care. Details are described below.

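### Table 1 scores a Mentor Mother checklist as complete at 4 of 6 steps and divides checklists by Mentor Mothers, so the fidelity figure cannot show delivery as planned

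*Protocol article*

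**What the plan says.** The fidelity indicator is in the Implementation block of Table 1 (protocol article, Conceptual Frameworks). Its three parts are:

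- Description: the "proportion of complete MM checklists completed by MMs at 6 months", presented as fidelity to the intervention as planned.
- Numerator: "Number of checklists showing 4 of 6 steps completed for each MM encounter".
- Denominator: "All MMs who have seen at least 12 weeks of service at 6-month follow-up".

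The data sources are Mentor Mother (MM) logs and employment records, and the timing is 6 and 18 months. The article does not list the six steps, name any as mandatory, or give a reason for the cut-off of 4.

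Three other places bear on the point:

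- MoMent HIV+HCC Adapted Intervention gives the MM duties, which end with "returning testing results and facilitating treatment for WLWH who need follow up care".
- Major Change 2, in the Aim 1 text, records that "High-risk HPV results were determined better returned by MMs rather than by nurses". It is one of two key changes that came out of the stakeholder conference.
- A separate Implementation row counts the "Number of WLWH treated within 2 weeks of SC sample received at clinic", among women positive for HPV 16/18/45.

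**The concern.** Fidelity is one of the four properties that Aim 2 sets out to assess. A reader who sees a high proportion of complete checklists will take it that the programme was delivered as designed. The numerator does not support that reading, because a third of the steps (2 of 6) may be absent and the checklist still counts. All steps carry equal weight, so the indicator cannot tell a trivial omission from a central one.

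The practical risk lies in interpretation. If uptake or follow-up turns out poor, the team will need to know whether the programme failed or was not delivered. An indicator that accepts partial delivery as complete makes that harder to judge.

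The row also has a unit problem. The numerator counts checklists and the denominator counts people, so the calculation does not give the proportion that the description promises.

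**Working it through.** The article gives no fidelity value, target or sample size for this row, so there is no figure to reproduce. The check is on the definition.

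**1. What the 4-of-6 rule accepts.** Six steps, each done or not done, give 2^6 = 64 patterns. Read as at least 4, the rule passes C(6,4) + C(6,5) + C(6,6) = 15 + 6 + 1 = 22. Full delivery is 1 of 64. Read literally as exactly 4, it would pass 15 patterns and exclude the fully completed checklist, which cannot be intended.

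**2. What happens to any two named steps.** Both are present in a passing pattern when at least 2 of the other 4 are done: 6 + 4 + 1 = 11 patterns. So 22 − 11 = 11 passing patterns lack at least one of the two. Exactly 1 lacks both, with the other four done. Every checklist could follow that one pattern and still count.

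**3. Illustration of size.** Assume that steps are done independently, each with probability q. The rule then reports P(X ≥ 4) = 15q⁴(1−q)² + 6q⁵(1−q) + q⁶, and full delivery is q⁶. The values of q are assumptions and do not come from the article.

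| q | At least 4 of 6 | All 6 |
|---|---|---|
| 0.6 | 54.4% | 4.7% |
| 0.7 | 74.4% | 11.8% |
| 0.8 | 90.1% | 26.2% |
| 0.9 | 98.4% | 53.1% |

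These percentages use checklists as the denominator, as the row's description implies but its denominator column does not.

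**4. The row as written.** The plan has 30 MMs and 1500 women. With one qualifying checklist per woman, and all 30 MMs meeting the 12-week condition, the row gives 1500 / 30 = 50 checklists per MM. That is an average count, not a proportion.

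**5. Whether another row fills the gap.** Two rows come near. The treated-within-2-weeks row measures the timing of clinic treatment among women positive for HPV 16/18/45. It does not record whether an MM returned a result, and it leaves out women who are negative or positive only for other high-risk types. The performance-review row scores MMs, not delivery to each woman. No Table 1 row isolates return of results by MMs.

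**The case against.** The strongest objection is that the six steps are not shown. A reader might infer that fidelity can read 100% although results were never returned and treatment never facilitated. The article does not support that, for two reasons. First, nothing says that these duties are checklist steps. The listed duties come to six only if recruiting and enrolling are counted apart. The numerator also refers to each encounter, which may mean steps within one visit, and results reach the woman at a later contact than the sample collection. Second, a ceiling of 100% needs a checklist denominator, which the row does not give. Both objections stand, so the consequence is possible but not shown.

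A threshold below six may also be a deliberate allowance for steps that do not apply, since facilitation of treatment is irrelevant to an hrHPV-negative woman. This is fair as far as it goes. If the steps are the listed duties, however, it explains one step and not two: Recruitment of WLWH has the MM return and counsel on negative results as well. A flat cut-off would also excuse the step for women to whom it does apply.

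Gross failure would not be invisible either. Untreated women positive for 16/18/45 would show in the treatment row. Aim 2 also lists treatment of women with hrHPV as a key outcome. Eighty women are to be followed through the process with each step timed. The Aim 2 text adds a further source: "We will gauge implementation fidelity as indicated by peer leaders" through their progress reports. This lowers the stakes but does not reconcile the row's label with its rule.

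Finally, the step probabilities in the illustration are invented, and the article ties no test or decision to the fidelity figure. Both are true, and the table shows only how far apart the two definitions can lie.

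**Conclusion.** The point holds, and it is minor. Two defects are on the page and need no assumption beyond reading the cut-off as at least 4. The label says complete while the rule accepts any two missing steps, and the numerator and denominator are in different units. A high value would therefore not show delivery as planned.

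The size of the gap in this trial is unknown. The illustrative range, 98% against 53% at q = 0.9 and 54% against 5% at q = 0.6, rests on equal, independent step probabilities. The link to return of results is conditional. If that step is on the checklist, this indicator could miss its omission. If it is not, Table 1 has no measure of a key adaptation. The claim that results could go unreturned under a fidelity of 100% goes beyond what the article establishes.

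**What to change.** Redefine the Table 1 row, here or in the analysis plan:

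- **Denominator:** checklists or encounters logged by MMs with at least 12 weeks of service.
- **Numerator:** those with all applicable steps done. List the six steps and state when each applies. If facilitation of treatment is one of them, it applies only to hrHPV-positive women.
- **Per-step reporting:** completion of each step separately, overall and by state. If return of results is not among the steps, report it as its own line.
- **4 of 6:** keep only as a secondary figure labelled partial delivery.

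The cost is a change of wording. MM logs are already the data source, so no new collection appears to be needed, provided that the checklist records each step individually. The downside is a lower headline fidelity figure.

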**FIGURE 1 F1:**
[figure not shown]
Aim 2 implementation flow chart (CHESS: Community, Home-based Education, Screening Services, Nigeria, 2025).

We will implement the adapted MoMent HIV+HCC program in 15 Nigerian clinical sites to recruit 30 MMs and 1500 WLWH for mid- and post-implementation assessments of reach, effectiveness, adoption, and fidelity. Implementation outcomes will be evaluated 6 months post-implementation with mixed methods. Key outcomes include reach and effectiveness, as indicated by eligible women touched by the HIV+HCC intervention, uptake of screening, women with high-risk HPV (hrHPV) 16/18/45/other genotypes treated, persistent or recurrent hrHPV post-treatment, and correlation of disease persistence with CD4 count and HIV viral load. We will measure program adoption outcomes that include training of MMs, WLWH who return a SC sample, and participating clinics’ integration of MoMent HIV+HCC into routine practice. We will gauge implementation fidelity as indicated by peer leaders’ progress reports. We will also measure system barriers and added cost of CC screenings.

#### Site Selection

Fifteen PEPFAR-supported clinics across 8 Nigerian states were selected based on geographic diversity (including urbanicity), level of care, ownership, and patient volume, to represent the diversity of care settings in Nigeria. Each site aims to recruit 100 WLWH aged 25–50.

#### MoMent HIV+HCC Adapted Intervention

The MoMent HIV+HCC adapted intervention will consist primarily of MMs supporting WLWH in testing for hrHPV. MMs will be responsible for recruiting and enrolling WLWH into the study, educating them about HPV and SC, transporting samples to the clinic/laboratory, returning testing results and facilitating treatment for WLWH who need follow up care. Details are described below.

#### Clinical Follow Up and End Points

hrHPV negative WLWH will be counselled to repeat the HPV test in 3 years and counselled that a negative result does not indicate future protection from HPV.

All WLWH who test positive for hrHPV 16/18/45/other will undergo visual inspection with acetic acid (VIA). Patients with acetowhite lesions after application of 3%–5% acetic acid per VIA protocol [31] will have these areas biopsied for diagnosis. Those who do not demonstrate acetowhite lesions on VIA (VIA-negative) will have 4 quadrant biopsies on the cervix along the squamocolumnar junction. For patients where the squamocolumnar junction is not fully visualized secondary to being in the endocervical canal, an endocervical curettage will be collected. If the patient qualifies for thermal ablation treatment, she will receive same-day treatment. However, if the lesion is ineligible for thermal ablation, the patient will be referred for excisional procedure for diagnosis and treatment. VIA, biopsies, and treatment will be performed by the clinic gynaecologist and biopsies will be sent to the state pathology laboratory.

All hrHPV WLWH treated per the protocol will repeat a self-test for HPV at 1 and 2 years from the time of treatment to determine clearance/persistence of hrHPV infection. If the WLWH is positive for hrHPV at 1- or 2-year post treatment, they will undergo VIA and biopsies and, based on the gynaecologist’s recommendation, repeat thermal ablation if eligible, or excisional treatment.

All test and treatment outcomes will be correlated with the CD4 count and viral load of the participants. As will be specified in consent forms, all left over aliquots from all cases of positive hrHPV, pathology blocks, and slides will be archived for future relevant studies. The HPV SC samples will also be available for full HPV genotyping.

#### Recruitment of Mentor Mothers (MM)

We will use purposive sampling techniques to select 30 HIV+HCC MMs from among existing MMs in the 15 selected facilities. Two MMs will work at each site and share responsibility for 100 WLWH. MMs will provide counselling and support, encourage clients to uptake the CC screening, facilitate the screening process, return HPV results, and provide support services for necessary treatment. Selected MMs will demonstrate: (1) 4+ years’ experience as an MM, (2) sustained viral suppression, (3) good adherence to drugs and clinic appointments, (4) history of advocating for people living with HIV, (5) history of returning patient logs, and (6) experience with CC screening.

#### Training MMs for the Adapted HIV+ HCC Program

Two MMs, a senior MM and a junior MM, as defined by length of time working as an MM at that clinic, were selected for participation in the CHESS study. The senior MMs were invited to a two-day, interactive training. Training included an overview of the CHESS project and information on HPV, CC screening, and project-specific MM responsibilities. MMs conducted their own HPV SC test using the Evalyn Brush tool [32] (HPV results were returned privately to each participating MM). MMs completed pre- and post-training assessments and were required to demonstrate proficiency (>80% correct responses) across all topics or require retraining.

Senior MMs who participated in the in-person training returned to their clinic and trained the junior MMs using study-provided workbooks and materials. Further, an online refresher training was held 3 weeks prior to the start of study implementation to review all study elements with all MMs and clinic site managers.

